### Study procedures

An overview of the study procedures and activities is summarised in table 2 and figure 3.

**Table 2 BMJOPEN2016014780TB2:** Outline of study visits

Study time point	Visit by	Activities
Recruitment	Peer educator	▸ Peer educator discusses study with potentially eligible participant and refers them to study staff
Enrolment	Research assistant	Assessment of eligibility Informed consent (if eligible) Baseline quantitative survey Baseline qualitative survey (∼5%)
Randomisation	Research assistant	▸ Randomisation of peer educator and their cohort of participants once all group members are enrolled
Intervention visit 1 (week 0)	Peer educator	Group-based intervention HIV prevention counselling and distribution of condoms Training on HIV self-test use (in HIVST arms) Distribution of HIV self-tests or coupons (in HIVST arms)
Intervention visit 2 (weeks 2–3)	Peer educator	Screening for adverse events Discussion of any difficulty with HIV self-test use (in HIVST arms) Referral to care and standard HIV testing Distribution of condoms
One-month visit (weeks 4–5)	Research assistant	One-month quantitative survey One-month qualitative survey (∼5%) Screening for adverse events
Intervention visit 3 (weeks 6–7)	Peer educator	Screening for adverse events Discussion of any difficulty with HIV self-test use (in HIVST arms) Referral to care and standard HIV testing Distribution of condoms
Intervention visit 4 (weeks 10–12)	Peer educator	Screening for adverse events Discussion of any difficulty with HIV self-test use (in HIVST arms) Referral to care and standard HIV testing Distribution of condoms Distribution of second HIV self-test or coupon (in HIVST arms)
Four-month visit (weeks 16–18)	Research assistant	Four-month quantitative survey Four-month qualitative survey (∼5%) Screening for adverse events HIV status assessment

HIVST, HIV self-testing.

**Figure 3 BMJOPEN2016014780F3:**
[figure not shown]
SPIRIT flow chart of study assessments. HIVST, HIV self-testing.

#### Peer educator visits

In all study arms, peer educators will meet with participants at least four times (approximately monthly) over the course of the study. The first peer educator intervention visit (intervention visit 1) will be a group-based visit, and includes simple HIV prevention information, information on where to go for HIV testing and condom provision. The initial group-based intervention is organised by the peer educator with assistance from the research assistant, and occurs in a private location of mutual convenience for the group members (such as a study office, or near a work place). In the HIVST arms, peer educators will provide a brief overview of how to use the self-test kits, whom to contact if participants have problems or concerns, and the importance of as well as how to obtain additional care, including confirmatory testing and linkage to care. Follow-up visits (intervention visits 2–4) with peer educators comprise brief one-on-one check-in visits, during which peer educators will distribute condoms, discuss any issues participants have with the HIVST kits or other elements of the study, and screen for adverse events including intimate partner violence. Between visits, peer educators will be available should participants need help with any issue relating to safe sex, HIV, violence or any other elements of the study. Peer educators do not specifically discuss HIV status with any participant unless the participant seeks out the peer educator for advice. Participants are given alternatives should they need help with HIVST or another element of the study but do not want to disclose their HIV status to the peer educator. In particular, participants in all study arms also have access to an anonymous 24-hour hotline provided via the study. Participants will be instructed by the research assistant that they can call the 24-hour hotline at any time if they have difficulty with using the HIV self-test kit, need counselling related to HIV testing or gender-based violence, or need any other form of assistance over the duration of the study.

#### Direct distribution arm

In the direct distribution arm, peer educators will directly distribute HIVST kits to participants during the first intervention visit. The HIVST kit consists of a single OraQuick in-home HIV self-test and instructions translated into English, Nyanja and Bemba. The instructions are a step-by-step pictorial and written guide for using the test and interpreting the results.

Peer educators offer a second HIVST kit to participants in the direct distribution arm at the fourth intervention visit. There is no HIV status requirement for distribution of a second test. The second test is distributed at the last peer educator visit, 3 months after the first, to minimise contamination of study arms.

#### Fixed distribution arm

In the fixed distribution arm, peer educators give participants a coupon which they can exchange for an HIVST kit at a participating fixed distribution facility. These facilities include drug stores and health posts that have agreed to participate in the study and have received basic training on HIVST. Staff at the fixed distribution points collect the coupons when they are exchanged for an HIVST kit and give them to research staff on a weekly basis. These coupons include a bar code that is scanned by study staff to record which participants collected the HIVST kit.

Peer educators offer a second coupon to participants at the fourth intervention visit to individuals, similar to the direct distribution arm, which can be used to obtain the second HIVST kit.

#### Standard of care arm

In the standard of care arm, peer educators give participants information about existing HIV testing services where participants can go for testing. In Livingstone, Chirundu and Kapiri, available options generally include government facilities, non-profit faith-based facilities and private facilities. While clinics designed specifically for FSWs were previously in operation in these cities, funding constraints forced these facilities to close in 2015. The information that participants receive about HIV testing facilities is customised to the city of their recruitment, and identical information is given to participants in each of the three arms.

In all study arms, participants will receive a linkage to care card from their peer educator that they will be requested to bring if they seek confirmatory testing and HIV care.

### Data collection

#### Baseline survey: enrolment

At the enrolment visit, all participants complete a quantitative questionnaire administered by a research assistant. Quantitative data are collected directly on a tablet. All assessments are conducted in a private room at a time and location that is convenient to the participant. The baseline survey covers broad topics including demographics and household composition, sex work and professional history, reproductive health and contraception, sexual behaviours, HIV testing history, attitudes towards HIVST, access to healthcare, and measures of substance use,^21^ depression,^22^ social support, self-efficacy,^23^ and empowerment.^24^

#### One-month and 4-month visits

Follow-up surveys will be conducted at the 1-month and 4-month visits from intervention visit 1 (see table 2). As with the baseline survey, all quantitative data will be collected via a tablet, and qualitative data (4-month visit only) are collected via an audio recorder. Participants in all arms of the study will be asked about their recent HIV testing history, sexual behaviours, access to healthcare and linkage to care. In the HIVST arms of the study, participants will additionally be asked about their experiences with the HIVST kit, including if they used it and details about their experience using the test, as well as their experience with the peer educator. Participants in all arms are asked again at 1 and 4 months about HIVST acceptability and perceived likelihood of using such tests in the future.

#### Qualitative interviews

Approximately 5% of the sample (15 participants per arm, 45 in total) are randomly selected at baseline to participate in individual qualitative in-depth interviews. During baseline screening, a random subset of participants will be asked if they would be interested in participating in the qualitative phase of the study. Individual in-depth interviews are conducted by trained research assistants at baseline and at the 4-month follow-up visit (table 2). All qualitative data are collected via an audio recorder. Baseline interviews explore community norms related to HIV testing, multilevel (including individual, structural and interpersonal) barriers to accessing HIV testing and other healthcare, experiences in sex work, and baseline perceptions of HIVST. At follow-up, qualitative interviews focus on experiences using the HIV self-test for individuals who are in one of the two intervention arms, and individuals in all arms will be asked about their perceptions of the HIV self-test and how HIVST might be implemented at scale. In all arms at follow-up, the interviews will explore empowerment and self-efficacy related to HIV testing and HIV status disclosure.

### End point measurement

Study effectiveness and safety end points are summarised in table 3. The primary effectiveness end point for the study is the proportion of participants who tested in the previous month as assessed at the 1-month follow-up visit. Secondary effectiveness end points include testing at 4 months, awareness of HIV status, HIVST kit use (restricted to the HIVST arms), linkage to care and adverse events. Safety end points include intimate partner violence and mental health.

**Table 3 BMJOPEN2016014780TB3:** Summary of study end points

End point	Operationalisation
*Primary effectiveness end point*	
Tested for HIV in the past month	Recent HIV testing measured by asking participants when they last tested and where (in all arms of the study)
*Secondary effectiveness end points*	
Use of HIV self-test	Measured by buying back unused HIV self-tests at the 4-month visit
Awareness of HIV status	Measured using a three-step approach: (1) asking participants if they know what their status is; (2) offering participants a small financial gift if they can correctly tell the interviewer what their HIV status is; 3) confirming HIV status with a rapid test
Linkage to care and confirmatory testing	Measured in two ways: (1) during follow-up visits, asking participants if they received confirmatory testing and linked to care; and (2) collection of referral cards linking individual HIV self-tests to individuals via a unique identification number
Sexual behaviours	Measured via CAPI, including number of sexual behaviours, event-level sexual behaviour data, and condom use with primary and casual partners
*Safety end points*	
Misuse of HIV self-tests	Including difficulty conducting the test (ie, mistakes in taking the test, incorrect use of components of the test), difficulty reading the test Identified through interview and ongoing consultation with peer educators
Intimate partner violence	Measured through surveillance and interviews by research assistants Any intimate partner violence (including verbal, physical or sexual) will be documented and reported

CAPI, computer-assisted personal interview.

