#### Recent HIV testing

Recent HIV testing is assessed by self-report at the 1-month and 4-month visits. Participants are asked when their last HIV test was, and then asked where their test was to determine if their last test was an HIVST or other.

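### The one-month look-back of the primary end point can be shorter than the time from kit hand-out to the 1-month visit, so the earliest tests may not count

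*Protocol article*

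**What the plan says.** The End point measurement section defines the primary effectiveness end point as "the proportion of participants who tested in the previous month as assessed at the 1-month follow-up visit". The Recent HIV testing section says how it is obtained, by self-report: "Participants are asked when their last HIV test was", followed by a question on where. The article does not give the month in days, and it does not say that every test since the intervention began counts.

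The timing comes from other sections. Table 2 under Study procedures has the entries "Intervention visit 1 (week 0" and "One-month visit (weeks 4–5", both in weeks. The follow-up clock starts at the first of these: "Follow-up surveys will be conducted at the 1-month and 4-month visits from intervention visit 1". In the direct arm, "peer educators will directly distribute HIVST kits to participants during the first intervention visit". In the fixed arm, "peer educators give participants a coupon which they can exchange for an HIVST kit at a participating fixed distribution facility". Standard-of-care women are told at the start where existing testing services are, and women in the other two arms receive the same information.

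**The concern.** The look-back has no slack, but the visit window runs past one month. Take a direct-arm woman who tests on the day she gets the kit and is interviewed on day 35. Her last test was 35 days ago, so under the stated rule she has not tested in the previous month. She has nevertheless done what the intervention was meant to achieve.

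The tests at risk are those made soonest after hand-out. A direct-arm woman can test on day 0. A fixed-arm woman must first redeem a coupon, and a standard-of-care woman must go to a testing service. If early tests are lost more often where access is quickest, direct versus control and direct versus fixed would both be biased against direct distribution. The Specific aims section names both comparisons.

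**Working it through.** **Inputs.** From Sample size considerations: 300 per arm, 50 clusters per arm, 20% loss to follow-up, intracluster correlation 0.03, control rate 50%, risk ratio 1.30 (hence 65%), type I error 0.05, stated power 89%. From Table 2: hand-out at week 0, visit at weeks 4–5. Assumptions: a two-sided test; a month of 28, 30 or 31 days; visits spread evenly over days 28–35, or over days 28–41 if week 5 is counted to its last day.

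**The plan's own figure.** Analysed per arm: 300 × 0.8 = 240. Mean cluster size: 240/50 = 4.8. Design effect: 1 + (4.8 − 1) × 0.03 = 1.114. Effective n: 240/1.114 = 215.4 per arm. For 50% versus 65%, the pooled standard error is √(2 × 0.575 × 0.425/215.4) = 0.0476 and the unpooled one is √((0.25 + 0.2275)/215.4) = 0.0471. Then z = (0.15 − 1.96 × 0.0476)/0.0471 = 1.20, which gives power 88.6% (89.0% with unpooled variance throughout). The stated 89% is reproduced.

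**The gap.** For a visit on day *v* and a month of *W* days, the uncovered time after hand-out is max(*v* − *W*, 0). The share is the fraction of permitted visit days on which a day-0 test falls outside the look-back.

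| Month (days) | Visits days 28–35: largest gap; share | Visits days 28–41: largest gap; share |
|---|---|---|
| 28 | 7 days; 7/8 = 87.5% | 13 days; 13/14 = 93% |
| 30 | 5 days; 5/8 = 62.5% | 11 days; 11/14 = 79% |
| 31 | 4 days; 4/8 = 50% | 10 days; 10/14 = 71% |

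A visit on days 28–30 with a 30- or 31-day month loses nothing.

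**Illustration of size.** Take 65% and 50% as the true proportions tested since intervention visit 1. Assume one test per woman and exact recall. If *F* is the distribution of time to test, the share of tests lost at a visit on day *v* is *F*(*v* − *W*)/*F*(*v*), averaged over visit days. Let control tests fall evenly over follow-up, and use a 30-day month with visits on days 28–35.

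- Control loss: (1/31 + 2/32 + 3/33 + 4/34 + 5/35)/8 = 5.6%, so the observed rate is 0.50 × 0.944 = 47.2%.
- Kit use even over 28 days: direct-arm loss is (1 + 2 + 3 + 4 + 5)/28/8 = 6.7%, so the observed rate is 60.6%, the risk ratio 1.285 and power 80%.
- Early kit use (exponential, mean 7 days): direct-arm loss is 21%, so the observed rate is 51.3%, the risk ratio 1.09 and power 13%.

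With a 31-day month the same two cases give risk ratio 1.29 with power 83%, and 1.15 with power 33%. With a 30-day month and visits up to day 41, even kit use gives 1.24 with power 57.5%.

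**The case against.** The best defence is that the article does not define a month in days and does not show how answers are coded. A one-month look-back at a visit timed one month after hand-out suggests that the look-back was meant to cover the follow-up interval. A full protocol, questionnaire or analysis plan may say so. Women who answer that they tested about a month ago may be counted, and a later test, such as a confirmatory test or one prompted by the referral at weeks 2–3, brings a woman back into the window. All of this stands, and it limits how much would be lost. It does not remove the mismatch: the stated end point and the stated visit window do not fit as written. In an unmasked trial, coding of borderline answers should not be left to the interviewer.

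A reader might infer that many direct-arm women will be scored as not tested, or that the loss falls mainly on that arm. The documents support neither as fact. Table 2 gives a permitted window, not a distribution of visits. No time-to-use data are given, and all arms receive testing-site information at the start, so early tests can be lost in every arm.

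A reader might also infer that the 89% power is wrong. It is correct on its inputs. The sample size section states its 50% and risk ratio for the end point as written, so those rates may already reflect the look-back. Deducting losses from them is an assumption made for illustration.

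**Conclusion.** The point holds as a mismatch between the end point and the visit schedule. Following the stated rule can drop the earliest tests after the intervention and so understate testing. The direction against direct distribution is a reasonable inference from the order in which the arms gain access, not a documented result.

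The gap in days follows from the schedule once a month length is chosen. The effect on risk ratio and power does not, because it depends almost wholly on the assumed timing of tests. With similar timing in both arms the risk ratio barely moves (1.285 against 1.30), and power falls mainly because the absolute difference shrinks from 15 to about 13.4 points (60.6 − 47.2). With much earlier use in the direct arm, most of the contrast could disappear.

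This should be fixed before analysis, since it decides who counts as a primary responder. It does not invalidate the end point and is not a bar to the trial.

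**What to change.** Define the primary end point as any HIV test, of any type, from intervention visit 1 to the 1-month interview, applied alike in all three arms. Make sure the question on the last test records the answer relative to intervention visit 1, either as a date or as before or after that visit. The article says only that women are asked when they last tested, so a date may not be available now. Keep the literal past-30-days definition as a sensitivity analysis.

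The cost is a change to the end point wording and the derivation code, and a small questionnaire change if answers are now recorded in coarse intervals. The drawback is that the period counted varies between about 4 and 5 weeks (nearly 6 if all of week 5 is used), but alike by design in all arms. If the planning rates of 50% and 65% apply to that period, the stated power is unchanged.

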#### Recent HIV testing

Recent HIV testing is assessed by self-report at the 1-month and 4-month visits. Participants are asked when their last HIV test was, and then asked where their test was to determine if their last test was an HIVST or other.

#### HIV status knowledge

Correct reporting of HIV status via a self-report is subject to social desirability bias. To accurately measure whether an individual knows their HIV status, they must both correctly report knowledge of their HIV status and be willing to take an HIV test. To overcome some of the bias in ascertaining self-reported HIV status, we use a three-step approach. First, participants are asked if they know their current HIV status. They are then asked to tell the research assistant their current HIV status, and are told to take their best guess if they do not know. Participants are then asked to take a rapid HIV test, and are counselled that this test is entirely voluntary. To reduce bias in self-reporting HIV status, participants are told that they will receive a small gift (worth ∼US$1) if they correctly report their status. However, after the assessment, all participants will receive the gift regardless of their reported status; thus, the cash transfer is perceived as conditional but is actually unconditional for ethical reasons. Pretest and post-test counselling will be available to all individuals who participate in the HIV status assessment. This assessment is performed only at 4 months.

#### HIVST kit use

Actual use of the HIVST kit may also be subject to social desirability bias. Participants may want to report that they used the HIVST kit when they did not for many reasons, including a desire to please the researchers, a sense of obligation or misperception about what it means to use the test.^25^ As an attempt to reduce bias in ascertainment of actual use of the HIVST kits, research assistants will ask participants to buy back any unused HIVST kits at the end of the study with the justification that the study has now reached completion. Participants will be offered ∼US$1 in exchange for any unused test kits in their original packaging. Prior to this offer, participants are not told that researchers will buy back tests at the end of the study (this information is also not included in the informed consent). To avoid gossip among study participants, the first buy-back will not happen until at least 1 month after the last test kit has been distributed (with the assumption that all participants would have used the test kit at that point if they were planning to).

#### Stigma and empowerment

Stigma and empowerment are measured both quantitatively and qualitatively at baseline and 4 months. Empowerment is measured additionally at 1 month. Quantitatively, sex work stigma is measured via a six-item scale that covers enacted, perceived and self-stigma,^26^ and HIV stigma is measured by a nine-item scale measuring attitudes towards individuals living with HIV.^27^ Qualitatively, stigma measurements include questions related to barriers to accessing care, interactions with police and experiences working as a sex worker. We hypothesise that at baseline individuals who report a greater amount of stigma will have reduced HIV testing, and that these individuals will have greater uptake of HIVST. Empowerment is defined as the process by which disenfranchised individuals acquire the ability to make choices.^24^ Quantitatively, empowerment is measured with a five-item scale addressing sex worker agency and power within.^24^ Qualitatively, empowerment is measured as the ability to get things the participant needs, to change her situation and control over elements such as condom use. We hypothesise that access to HIVST will lead to an improved sense of empowerment.

#### Adverse events

Adverse events are monitored and documented throughout the study. The primary adverse events of concern are psychological harm as a result of use of the HIV self-test (eg, if participants test positive for HIV and are not prepared for the results). Although UNAIDS has recently indicated no evidence of serious adverse events related to HIVST (ie, self-harm, violence or human rights violations),^28^ occurrence of any such events are reported to all principal investigators and the SOC within 24 hours of study staff becoming aware of them. Other adverse events include c oercive testing or unintentional or unauthorised disclosure of HIV status, which are similarly reported within 24 hours.

